## Ethical approval

Ethical approval was obtained for both QUICK studies [8].

## Discussion

Recent prevalence data from National Surveys indicate that many risk factors for CVD are highly prevalent in Nigeria: alcohol abuser/dependant - 4.4% (M - 8.1%, F - 0%); overweight/obesity (BMI ≥ 30 kg/m^2^) - 13.9% (M - 5.5%, F - 21.1%); physical inactivity - 6.8%; tobacco use - 9.9% (M - 19.3%, F - 1.8%); raised cholesterol - (M - 10.4%, F - 21.6%); raised blood pressure (systolic ≥ 160 mmHg or diastolic ≥ 95 mmHg) - 12.4% (M - 12.1%, F - 12.7%); and diabetes - 2.8% (M - 2.7%, F - 3%). There are no data on dietary intake such as fruits and vegetables http://www.who.int/research/en/. A substantial majority of CVD are preventable or treatable if patients at risk have access to quality CVD prevention and care programs. Quality care is, however, mostly inaccessible in resource-limited settings. Even where such care may be available and accessible, strict compliance and adherence to the dictates of therapy regimes becomes paramount for the successful control of CVD risk factors, and prevention of CVD in the affected populations. A recent study in Kwara state, Nigeria where QUICK is being implemented concluded that control of hypertension is unacceptably poor because of poor knowledge of hypertension and adverse practices by patients [17]. In a similar vein, another Nigerian study suggested that physicians should allocate special time for health education, having concluded that lack of time by physicians and inadequate knowledge about hypertension by patients are some of the potent barriers to effective CVD prevention and care [18]. Furthermore, with particular reference to SSA where deep routed cultural practices still play prominent roles in people's lives, health education to prevent CVD must be patient centered, and developed with due consideration for socio-cultural relevance in order for the intervention to be successful. By researching into the most optimal methods to implement an appropriately developed cardiovascular health education program, our expectation is that the present study will provide insight into, and contribute substantially to the improvement in CVD management and outcomes. We hope that the envisaged intervention, CHEP, will become productively applicable not only in Nigeria, but also in other similar settings in SSA and across the globe.

The study has one notable limitation:

The design of our evaluation of CHEP could have been improved by using a control group and a randomized design. However, the study is conducted in a very specific context, where it is impossible to avoid contamination. For example, patients have generally long waiting hours and may communicate about their condition or the treatment with each other. Moreover, the number of health care professionals in the clinic is limited such that it would be impossible to randomize them into a control and experimental condition. In addition, given the context of the community health insurance program, other clinics that provide standard cardiovascular care are difficult to find in the region. Nevertheless, to address this limitation, we consider analyzing the data collected during QUICK - I study for the patients included in QUICK - II to further compare and evaluate the effects of CHEP.

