## Methods

### Project design

#### QUICK - II consist of two consecutive parts

In *part 1 *of the study, we will develop a stakeholder based Cardiovascular Health Education Program (CHEP) that is to be used to educate patients at risk of CVD who are enrolled in a private health insurance plan in rural Nigeria. To develop CHEP, we will use the following step-wise approach: (i) open qualitative interviews will be conducted with key stakeholders in CVD care to explore their perceptions on CVD, CVD risk factor management and CVD prevention and care. These stakeholders include patients at risks for CVD, healthcare providers (HCP), and health insurance managers of HCHP; (ii) on the basis of the outcomes of interviews with patients, CHEP will be developed; (iii) supportive strategies needed to implement CHEP successfully will be identified on the basis of the outcomes of the interviews with HCP and health insurance managers.

In *Part 2 *of the study we aim to evaluate the effect of CHEP through a prospective hospital-based study, using a pre-post intervention design. Measurements will be conducted in a subset of patients included in QUICK - I: those who have uncontrolled hypertension or other CVD risk factors, or are non adherent to medication after 12 months of treatment.

In addition, case file data will be reviewed and interviews with health care professionals in the participating clinic will be held and analyzed to evaluate the feasibility of the application of CHEP in practice.

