## Part 2: Evaluation of Chep

### Study population

To be included in the evaluation study of the effect of CHEP (part 2), patients have to meet the following inclusion criteria. They must: (i) be enrolled in HCHP; (ii) be registered as a patient in OOH; (iii) be included in the QUICK - I study for at least 12 months; (iv) have a diagnosis of hypertension; (v) have uncontrolled BP (≥140 mmHg systolic or ≥90 mmHg diastolic) or be non adherent to prescribed medication or any other recommended life style changes according to their score on the Morisky scale [14]; and (vi) be ≥18 years of age. Patients who meet these inclusion criteria will be excluded if their treating health care professional judges them unfit for participation (e.g. due to co morbidity) or if they are not capable or unwilling to give informed consent. Female patients who are pregnant or lactating will be excluded from the entire study because the etiology, prognosis and treatment regimes of gestational diabetes and pregnancy-induced hypertension are different compared to hypertension and diabetes in non-pregnant women.

To be included in the qualitative interviews for the feasibility analysis, healthcare professionals must: (i) be a HCP in OOH who participated in the implementation of CHEP, or be managers and doctors of HCHP; and (ii) give informed consent.

Table 1 shows an overview of the inclusion and exclusion criteria for CHEP study. For an overview of the inclusion and exclusion criteria of QUICK - I, see the article of the QUICK - I study design [8].

**Table 1 T1:** Inclusion and exclusion criteria for CHEP study.

Inclusion Criteria	Exclusion Criteria
Patients:	Patients:
• Enrollment in HCHP	• Unwillingness to give informed consent
• Registered and accessing care in OOH	• Unfit for participation (e.g. due to co morbidity)
• Inclusion in QUICK - I for at least 12 months	• Pregnant or lactating females
• Diagnosis of hypertension	
• Uncontrolled hypertension or non adherence to prescribed medication or lifestyle changes after 12 months in QUICK - I	
• Age of 18 years and over	
• Give informed consent	

Healthcare Professionals for interviews on feasibility of CHEP:	
• HCP of OOH who participated in the implementation of CHEP, or	
• Managers and Doctors of HCHP	
• Give informed consent	

Figure 1 describes the project populations for QUICK - II and their relationship to the QUICK - I study.

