#### Patient recruitment

The following steps will be applied in recruiting patients for the CHEP study:

1. Researchers will use the records of the QUICK - I study to identify all patients with uncontrolled hypertension or with low or medium adherence scores for medication or other life style measures on the Morisky Scale at 12 months after inclusion into the study.

2. Eligible patients will be informed about QUICK-II and invited for participation through a written invitation.

3. A research assistant will assess patients who are interested in participating for eligibility criteria and eligible patients will be asked to give informed consent.

4. Patients who give informed consent will be invited to a one-hour baseline assessment session.

5. Included patients who have completed baseline assessments will be invited to have three CHEP sessions spaced over a period of 4 months and one final assessment interview six months after baseline.

To encourage participation, all included patients will be reimbursed for extra travel costs incurred in visiting for assessments and CHEP sessions outside their normal clinic days.

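### The substitute proposed for a control group, the enrolled patients' own QUICK-I data, carries a regression-to-the-mean component favouring CHEP that the limitation paragraph does not mention

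*Protocol article*

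**What the plan says.** All references are to the Protocol article.

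- **Design.** Project design describes part 2 as a hospital-based study "using a pre-post intervention design". There is one group and no control.
- **Who enters.** The same section restricts measurement to a subset of QUICK-I: "those who have uncontrolled hypertension or other CVD risk factors, or are non adherent to medication after 12 months of treatment". Study population (Part 2), criterion (v), requires patients to "have uncontrolled BP (≥140 mmHg systolic or ≥90 mmHg diastolic) or be non adherent to prescribed medication or any other recommended life style changes". Patient recruitment (Part 2), step 1, takes this from QUICK-I records at month 12, to "identify all patients with uncontrolled hypertension or with low or medium adherence scores for medication or other life style measures on the Morisky Scale".
- **Baseline.** Step 4 creates a separate measurement after consent: "Patients who give informed consent will be invited to a one-hour baseline assessment session". Materials and Measurements and Statistical methods then use that baseline and the assessment 6 months later.
- **Outcomes.** The adherence score is primary and blood pressure is secondary (Outcomes, Part 2). Both are also selection variables.
- **Target.** Sample size calculation assumes 32% low, 52% medium and 16% high adherence, and a 10% shift to a higher category. Table 2 uses the same 10%.
- **Remedy for the missing control.** The Discussion concedes that a randomised control group would have been better and explains why one is not feasible. A single remedy follows, introduced by the words "Nevertheless, to address this limitation". The authors' statement is: "we consider analyzing the data collected during QUICK - I study for the patients included in QUICK - II to further compare". The stated purpose is to judge what CHEP achieves. The paragraph does not mention selection on the month-12 value or regression to the mean.

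**The concern.** A patient qualifies partly because of a persistently poor level and partly because of a chance poor reading at month 12. The QUICK-I series of the enrolled patients therefore ends on a value that selection has pushed in the bad direction. Their entry-to-month-12 change looks worse than that of the whole QUICK-I cohort, and later measurements drift back with no intervention. In a comparison of change during QUICK-I with change during CHEP, this component counts as benefit from CHEP.

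This is the only comparative evidence the article names for part 2, and it is offered expressly to make up for the missing control. A reader of the results could take a better change under CHEP than under QUICK-I as support for effectiveness when part of it comes from how patients were chosen.

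**Working it through.** The article gives no figure for this comparison, so there is none to reproduce. The sample size of 150 is not an input.

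**Inputs from the article.** Categories 32/52/16; a 10% upward shift as target, read here as 10 percentage points; entry on uncontrolled blood pressure or low/medium adherence at month 12.

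**Assumptions not in the article.** True adherence is stable and CHEP has no effect. Visit errors are independent. Reliability r is 0.6 to 0.9. The share p with uncontrolled blood pressure at month 12 is 40 to 60%, independent of adherence. The separate lifestyle score, a further entry route, is not modelled. It would admit more patients with high medication adherence and so reduce the figures for the medication score.

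**Model.** The observed value at visit t is √r·T + √(1−r)·e_t, with T the stable trait, cut at the 32nd and 84th percentiles. The four visits are QUICK-I entry, month 12, QUICK-II baseline and final. Net shift is the percentage moving up a category minus the percentage moving down. Three million patients were simulated for each r.

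**Step 1: selection on low/medium adherence only.** For r = 0.6, 0.7, 0.8, 0.9 the QUICK-I net shift S is −10.4, −9.0, −7.3, −5.2 points. Month 12 to QUICK-II baseline is equal and opposite to within 0.1 point. Baseline to final is zero to within 0.1 point.

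**Step 2: the actual 'or' rule.** Only patients with high adherence and controlled blood pressure are left out, a share of 0.16(1−p). The enrolled share is 1 − 0.16(1−p), that is 0.904 at p = 0.4 and 0.936 at p = 0.6. The whole cohort's net shift is zero, so the enrolled patients' shift is

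S × 0.84(1−p) / [1 − 0.16(1−p)].

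The multiplier is 0.504/0.904 = 0.558 at p = 0.4 and 0.336/0.936 = 0.359 at p = 0.6. The simulation gives the same results:

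| r | adherence only | 'or' rule, p = 0.4 | 'or' rule, p = 0.6 |
|---|---|---|---|
| 0.6 | −10.4 | −5.8 | −3.7 |
| 0.7 | −9.0 | −5.0 | −3.2 |
| 0.8 | −7.3 | −4.1 | −2.6 |
| 0.9 | −5.2 | −2.9 | −1.9 |

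**Step 3: the spurious contrast under the 'or' rule.**
- Before value = QUICK-II baseline: 0 minus the QUICK-I shift, so 1.9 to 5.8 points in favour of CHEP.
- Before value = month-12 record: the regression counts twice, so about 4 to 12 points.

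A second calculation used the share with high adherence and between-visit correlation 0.4 to 0.8. It gives 2.6 to 7.0 and 5.2 to 14.0 points respectively.

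**Step 4: blood pressure and net direction.** Assume entry mean SBP 155 mmHg, a real QUICK-I fall of 15, between-person SD 16, within-person SD w of 8 or 12, and selection at SBP ≥140 alone. Month-12 values then have mean 140 and SD σ = √(16² + w²), so the cut-off is at the mean. The mean error among those selected is (w²/σ) × 0.798:
- w = 8: 64/17.89 × 0.798 = 2.9; QUICK-I change −15 + 2.9 = −12.1.
- w = 12: 144/20 × 0.798 = 5.7; QUICK-I change −15 + 5.7 = −9.3.

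With no CHEP effect the later change is 0 from the QUICK-II baseline, or −2.9 and −5.7 from month 12. CHEP then looks worse than QUICK-I by 12.1 and 9.3 mmHg, or by 9.3 and 3.5 mmHg. Selection favours CHEP throughout, but an assumed real fall in QUICK-I outweighs it. Under the 'or' rule with no true change, SBP SD 20 and between-visit correlation 0.4 to 0.8, the SBP distortion over all enrolled is only 0.3 to 0.8 mmHg each way.

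**The case against.** Several points on the other side stand.

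- **The analysis is tentative.** It is only under consideration, it appears in the Discussion and not in Statistical methods, and no contrast or time window is given. The bias described belongs to a change-versus-change comparison, which is the natural reading but is not spelled out. Using the month-12 value against the QUICK-II baseline would also be an analysis of QUICK-I data in QUICK-II patients, so the sentence already allows the better use. This lowers the priority. It does not remove the point, because a specific comparator is named as the remedy and its known weakness is not.
- **A reader might infer that the comparison as a whole is biased in favour of CHEP.** The documents do not support that. Step 4 shows that a real fall in blood pressure during QUICK-I can make CHEP look worse, and regression from QUICK-I entry can act the same way. The QUICK-I entry criteria are in another paper.
- **A reader might infer that the artefact is as large as the effect sought.** About 10 points arises with adherence-only selection at reliability 0.6, or near the top of the range when month 12 is the before value. Under the stated entry rule with the separate baseline it stays below 10.
- **A reader might infer that the planned pre-post analysis is itself biased this way.** It uses the separate baseline session, and Step 1 gives a null change of zero from there. The eligibility check (step 3) comes before that session, and nothing in the text re-applies the cut-offs to the baseline measurement.
- **The adherence comparison may not be feasible.** It needs a Morisky score at QUICK-I entry. The article documents QUICK-I scores only at month 12.

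**Conclusion.** The concern holds in a limited form. The only stated substitute for a control relies on a series that ends on the value used to select the patients. Comparing its change with the CHEP-period change includes a regression-to-the-mean component in favour of CHEP, and the limitation paragraph is silent on it. For adherence the component is about 2 to 6 percentage points with the QUICK-II baseline, and about twice that with the month-12 record, against a 10-point target. These sizes rest on assumed reliability, an assumed share with uncontrolled blood pressure, and independence between visits and between the two criteria. None of these is documented.

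The selection component has a known sign, but the whole comparison does not. The planned baseline-to-6-month change is free of this mechanism in the model, provided the entry cut-offs are not applied to the baseline reading. Because the affected analysis is supplementary and tentative, this is a worthwhile and cheap correction, not a condition for the study to proceed.

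**What to change.** In the limitation paragraph and in the analysis plan:

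1. Do not use the enrolled patients' QUICK-I entry-to-month-12 change as the comparator.
2. Keep the QUICK-II baseline session as the before value, and state that the blood pressure and adherence cut-offs are not re-applied to that measurement.
3. Report the change from QUICK-I month 12 to QUICK-II baseline, before any CHEP session, beside the baseline-to-6-month change. It is a benchmark for regression to the mean without CHEP. It should not be subtracted from the CHEP change or presented as a control group.
4. Name regression to the mean as a limitation.

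An untreated QUICK-I comparator is not recommended. Recruitment identifies all qualifying patients and invites the eligible ones, so those left without CHEP would mainly be refusers or patients judged unfit.

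The cost is some wording and slightly more analysis. The month-12 records and baseline values will already be held. The apparent effect may be smaller than the QUICK-I comparison would have suggested.

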## Abbreviations

BMI: Body mass index; CHEP: Cardiovascular health education program; CVD: Cardiovascular diseases; DM: Diabetes mellitus; HCHP: Hygeia community health plan; HCP: Health care professionals; HIF: Health insurance fund; HMO: Health maintenance organization; HTN: Hypertension; ISH: International society of hypertension; OOH: Ogo oluwa hospital; QUICK: Quality improvement cardiovascular care Kwara; SSA: Sub Saharan Africa; WHO: World health organization.
